#### Phase III

##### Experimental arm

A total of 122 patients will be enrolled into this arm and undergo an induction CIRT boost to the residual gross tumor volume. The dose of the induction boost will be determined in Phase I of the trial. One week after the first fraction of the induction boost, a standard PRT (60 GyE in 30 fractions) with concurrent daily oral administration of TMZ at 75 mg/m^2^ will commence.

##### Control arm

A total of 121 patients will be enrolled into this arm and undergo standard PRT with concurrent daily oral administration of TMZ.

##### Serologic immune markers

To ascertain the specific immune response profile to the induction CIRT boost, all patients enrolled into the Phase III study will have their blood samples investigated before irradiation to establish the baseline profile of serologic immune markers (detailed in Table 2 and between the fifth and sixth fractions of PRT to determine the changing profile. Those who receive the induction CIRT boost will have an additional serologic marker detection between the last fraction of the boost and the first proton fraction. The overall Phase III schema is illustrated in Fig. 1.

**Table 2 Tab2:** Serologic immune markers of GBM

Marker	Function/correlative findings	Assay
Pro-inflammatory/anti-tumor		
IL-1β	Stimulates cytotoxicity; serum levels decrease during low-LET radiotherapy [55]	Serum ELISA
IL-6	Pro-inflammatory cytokine, defective expression from lymphocytes in patients with glioma [56]	Serum ELISA
TNF-α	Promotes cell-directed cytotoxicity; reduced levels are associated with GBM [57]	Serum ELISA
CD3+ lymphocytes	Direct immune-mediated cytotoxicity; increased levels are associated with prolonged survival [58]	Flow cytometry
CD8+ lymphocytes	Direct immune-mediated cytotoxicity, increased levels are associated with prolonged survival [58]	Flow cytometry
Anti-inflammatory/pro-tumor		
IL-4	Induces immunosuppression and tumor tolerance; high levels are associated with GBM [57]	Serum ELISA
IL-10	Induces immunosuppression and tumor tolerance; high levels are associated with GBM [57]	Serum ELISA
TGF-β	Promotes proliferation and immune escape of GBM [59]	Serum ELISA
Regulatory T cells	Secrete IL-10 and TGF-β, suppress CD8-dependent tumor-specific cytotoxicity, and elevated in peripheral blood of GBM patients [60]	Flow cytometry

*GBM* glioblastoma, *IL* interleukin, *TNF*-*α* tumor necrosis factor-α, *TGF*-*β* transforming growth factor-β, *LET* linear energy transfer, *ELISA* enzyme-linked immunosorbent assay

**Fig. 1 Fig1:**
[figure not shown]
Illustration of the overall schema of the Phase III of the current trial. In the Phase III, the GBM patients will be randomized to receive either **a** a CIRT boost followed by standard PRT with concurrent TMZ (experimental arm) or **b** standard PRT with concurrent TMZ (control arm). Each patient will undergo an assessment of their tumor response based on imaging and immunologic serum studies. *Multi-modal MRI includes MRS, BOLD, DWI, DTI, PWI, and MRI. *GBM* glioblastoma, *CIRT* carbon ion radiotherapy, *PRT* proton radiotherapy, *TMZ* temozolomide, *RT* radiotherapy, *MET/FET PET* C-methionine positron/18F-fluoro-ethyl-tyrosine positron emission tomography, *MRI* magnetic resonance imaging, *MRS* magnetic resonance spectroscopy, *BOLD* blood oxygenation level-dependent imaging, *DWI* diffusion-weighted imaging, *PWI* perfusion-weighted imaging

### Study objectives

#### Phase I

The primary objective is to determine the maximal safe induction CIRT boost dose.

#### Phase III

The primary objective is to detect an improvement in OS in those patients who received an induction CIRT boost with no additional toxicity. The secondary objectives are to determine the response rates, progression-free survival (PFS), and tumor response (based upon assessment with C-methionine/fluoro-ethyl-tyrosine positron emission tomography [MET/FET PET] or magnetic
resonance imaging [MRI] and detection of serologic immune markers).

### Patient selection

#### Inclusion criteria

Patients who meet all of the following criteria will be considered for recruitment into this trial:Histologically confirmed, unifocal, supra-tentorial primary AA or GBM;Residual, clinically measurable tumor up to 5 cm in the largest dimension assessed by postoperative MET/FET PET, MR spectroscopy (MRS), or MRI;Able to determine the *MGMT* promoter methylation status;Indication for adjuvant radiotherapy with concurrent TMZ administration;Age ≥ 18 years;Karnofsky performance score ≥ 60;Ability to understand the purpose and content of the clinical trial;Written informed consent with required signature prior to enrollment and initiation of the treatment.

#### Exclusion criteria

Patients who present with any of the following criteria will not be included in this trial:Patient’s refusal to follow the trial protocols;Severe pulmonary hypertension, cardiovascular disease, peripheral vascular disease, severe chronic heart disease, and other complications that may interfere with radiotherapy;Previous radiotherapy to the brain;Previous malignancy requiring cytotoxic therapy within 5 years prior to enrollment;No residual, clinically measurable disease observed on postoperative MET/FET PET, MRS or MRI;A time interval > 8 weeks between surgery and the initiation of radiotherapy;Not yet recovered from toxicities of prior treatments;Pregnant or lactating women;Participation in another clinical study or in an observation phase of a competing trial.

### Treatment assignment

The flow chart of this Phase I/III trial is illustrated in Fig. 2. Patients enrolled into Phase I of this trial will be assigned to groups of 3, and each group will receive a progressively increasing dose of induction CIRT boost until the safe dose is determined or the maximal dose of 18 GyE in 3 fractions is reached without ≥ grade 3 toxicities. Patients who later opt out of the study will be replaced by newly enrolled ones. Patients enrolling into the Phase III of this trial will be randomly assigned to either the experimental or control arm (1:1 randomization), as described above. Patients withdrawn from this phase will retain their randomization number, and new patients will be issued with a new randomization number.

**Fig. 2 Fig2:**
[figure not shown]
The flow chart of the current Phase I/III trial. In the Phase I, the maximal tolerable dose (MTD) of the induction CIRT boost will be determined. The MTD will then be used in the experimental t arm in the Phase III of this trial. The Phase III aims to determine the overall survival, progression-free survival, and tumor response. *GBM* glioblastoma, *AA* anaplastic astrocytoma, *DLT* dose-limiting toxicity, *CIRT* carbon ion radiotherapy, *PRT* proton radiotherapy, *TMZ* temozolomide

### TMZ dosing and schedule

Conventional oral chemotherapy with TMZ (75 mg/m^2^) will commence on the first day of PRT in both arms. TMZ will not be administered during the CIRT boost in the experimental arm so as not to suppress the desired shift towards an anti-tumor immune response and the effect against glioma cells that have infiltrated the brain parenchyma at a distance from the primary tumor site.

### Radiotherapy planning

Target volume delineation: Numerous studies have indicated that the use of MET/FET PET, MRS in conjunction with MRI was superior to MRI alone in determining the extent of malignant involvement [33–36]. Therefore, tumor areas presented on the MET/FET PET, MRS as well as the traditional contrast enhancement and fluid-attenuated inversion recovery (FLAIR) abnormality indicative of residual non-enhancing tumor (edematous FLAIR signal that does not resolve after surgical decompression) will be used to determine the gross tumor volume (GTV).

The clinical target volume (CTV) receiving 60 GyE irradiation (CTV60) will be delineated with a 0.5-cm margin expansion from the GTV and will be the principle planning target volume of PRT. During PRT, a secondary CTV of 50 GyE in total will be given. The CTV50 will be delineated with a 1.5-cm expansion from the GTV. The volumes, doses, and delineations are summarized in Table 3.

**Table 3 Tab3:** Target Volume delineations and radiotherapy planning of GBM and AA

Radiotherapy	Target volume	Delineation	Dose/fractionation	Minimal dose coverage
CIRT boost	GTV	MET/FET PET or MRS abnormality, contrast enhancement, FLAIR abnormality representing residual tumor	3.00-6.00 GyE × 3 Fx	95%
PRT	GTV	MET/FET PET or MRS abnormality, contrast enhancement, FLAIR abnormality representing residual tumor	N/A*	N/A*
	CTV60	GTV + 0.5 cm margin	2.00 GyE × 30 Fx	95%
	CTV50	GTV + 1.5 cm margin	1.67 GyE × 30 Fx	95%

*GBM*: glioblastoma, *AA* anaplastic astrocytoma, *CIRT* carbon ion radiotherapy, *GTV* gross tumor volume, *MET/FET PET* C-methionine/18F-fluoro-ethyl-tyrosine positron emission tomography, *MRS* magnetic resonance spectroscopy, *FLAIR* fluid-attenuated inversion recovery, *N/A* not applied, *GyE* gray-equivalents, *Fx* fraction, *PRT* proton radiotherapy, *CTV60/50* clinical target volume receiving 60/50 GyE irradiation

* N/A: Since the GTV of PRT is not a target volume to give prescription dose, so “N/A” is marked in these cells

CIRT and PRT planning: Radiotherapy will be planned using the Syngo treatment planning system (Siemens, Erlangen, Germany) and delivered using the IONTRIS intensity-modulated raster scan system (Siemens, Erlangen, Germany) as previously described [37]. Briefly, CIRT and PRT will be performed once a day, 5 days a week. The patient’s position will be verified using a craniofacial X-ray before radiotherapy, and set-up deviations of more than 2 mm will be corrected. CIRT is planned with RBE calculated using the local effect model (LEM). The RBE values of CIRT at 3, 4, 5, and 6 GyE will be 3.3, 2.9, 2.6, and 2.4, respectively.

### Clinical outcome assessments

#### Overall survival

The duration of OS will be calculated as the time between the pathological confirmation of GBM and the date of death from any cause. Patients who do not succumb to their disease or who are not lost to follow-up will be censored at the date of the last follow-up.

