#### Type I error rate and power

Time to death for any reason will be compared between the two arms in Phase III of this trial, using a two-tailed log-rank test at an overall type I error rate of 5%. The desired power is 80%. Sample size calculation is based on the unstratified log-rank test.

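### The overall-survival censoring sentence contradicts the any-cause death event and is unusable on either literal reading

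*Protocol article*

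**What the plan says.** Under Overall survival (Clinical outcome assessments), the protocol article gives the event and the time origin: "The duration of OS will be calculated as the time between the pathological confirmation of GBM and the date of death from any cause". The next sentence is the censoring rule: "Patients who do not succumb to their disease or who are not lost to follow-up will be censored", with the last follow-up as the censoring date. No other OS censoring rule appears in the article.

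The section Type I error rate and power again uses death from any cause: "Time to death for any reason will be compared between the two arms in Phase III of this trial, using a two-tailed log-rank test". Outcome analyses places the two looks at 96 and 192 OS events and analyses all randomised patients as assigned.

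The censoring sentence under Progression-free survival has the same construction about patients who are not lost, but leaves out the reference to the disease.

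Two further facts bear on the time origin. Histological confirmation is an inclusion criterion, so it comes before randomisation. One exclusion criterion is "A time interval > 8 weeks between surgery and the initiation of radiotherapy".

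**The concern.** The event sentence and the censoring sentence disagree about a patient who dies of something other than glioblastoma. The first counts an event. The second, taken at its word, censors the patient because he or she did not succumb to the disease.

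This matters because the arms differ in radiation intensity. The experimental arm receives a boost on top of the same 60 GyE, and Table 1 puts cumulative brain EQD2 at 67.2 to 92.4 GyE with a boost against 60.0 GyE without. The Phase III primary objective is better OS with no additional toxicity. If treatment-related deaths were more frequent with the boost, the literal rule would take them out of the efficacy endpoint. It would also change what counts towards the event totals that trigger the two analyses.

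The second half of the sentence, about patients who are not lost, is faulty in its own right: it does not say clearly what happens to those who are.

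**Working it through.** **1. The sentence applied to four kinds of patient**

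| Patient | Any-cause definition | Neither dead of disease nor lost | Strict logical or |
|---|---|---|---|
| Died of glioblastoma, not lost | event | event | censored |
| Died of another cause, not lost | event | censored | censored |
| Alive, in follow-up | censored | censored | censored |
| Alive, lost | censored when last known alive | no rule | censored |

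Both readings contradict the any-cause definition in the second row. The first reading also fails in the fourth row, and the strict reading in the first.

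**2. The plan's own event count**

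Inputs (Sample size calculation; Type I error rate and power): medians 16 and 24 months, two-sided 5%, 80% power, 1:1 allocation.

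- Hazard ratio = 16/24 = 0.667; its log is −0.4055.
- Schoenfeld events = 4 × (1.960 + 0.842)² / 0.4055² = 191. The plan states 192, so it reproduces (the rounded 0.67 would give 196).
- Power at 192 events = Φ(√192/2 × 0.4055 − 1.960) = Φ(0.849) = 80.2%. With the stated looks (0.003 at 96 events, 0.049 at 192), overall two-sided error is 0.0500 and power 80.1%.

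The 192 is a count of any-cause deaths and stands.

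**3. Bias if the sentence were applied literally**

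Let x and y be the shares of deaths not due to glioblastoma in the boost and control arms. With shares constant over time, the hazard ratio after censoring them is about the true any-cause ratio × (1 − x)/(1 − y). The documents give neither share; these are assumptions.

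| x | y | True 1.00 reads | True 0.667 reads |
|---|---|---|---|
| 5% | 5% | 1.00 | 0.667 |
| 5% | 0% | 0.95 | 0.633 |
| 10% | 5% | 0.95 | 0.632 |
| 10% | 2% | 0.92 | 0.612 |

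**4. Lost events with equal shares**

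Starting from 192 any-cause deaths, at a hazard ratio of 0.667:

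| Share censored | Events counted | Power |
|---|---|---|
| 2% | 188 | 79.4% |
| 5% | 182 | 78.2% |
| 10% | 173 | 76.0% |
| 15% | 163 | 73.6% |

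If the analysis waited for 192 counted events instead, the cost would be delay: 192/0.95 = 202 or 192/0.90 = 213 any-cause deaths would be needed.

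**5. Time origin**

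The 8-week limit is 56/30.4375 = 1.84 months. In 20,000 simulated trials per setting (122 against 121 patients, exponential survival, 36 months' accrual, analysis at month 60), a random 0 to 8 weeks of event-free time was added in both arms. Type I error was 4.9% with it and 5.0% without; power was 78.3% and 78.4%.

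**The case against.** The best reply is that nobody would apply the sentence literally. The any-cause event is stated twice: in the sentence just before and in the section on type I error and power. The parallel sentence for progression-free survival omits the reference to the disease, which suggests that the authors simply meant patients still alive. This stands as evidence of a drafting slip. A reader might infer that the plan has settled on censoring toxic deaths, and the documents do not support that. They support only that the stated rule conflicts with the stated event. Fatal toxicity would not go unreported in any case, since adverse events are summarised by severity and compared between arms.

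It can also be said that lost patients are covered, because a living patient who is lost has not succumbed to the disease. That is right under the strict reading, so the gap for lost patients is not certain. But the strict reading also censors glioblastoma deaths in patients who were not lost, so it does not rescue the sentence.

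A reader might take the 5% dropout (12 patients) under Anticipated duration of trial as the number left without a rule. That figure combines loss to follow-up with treatment discontinuation, and patients who stop treatment can still be followed for death. No separate figure for loss is given.

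**Conclusion.** The OS censoring sentence is wrong as written and should be corrected, because it governs the primary endpoint and no literal reading agrees with the any-cause event. The event target of 192 is unaffected.

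The numerical harm is conditional. Bias towards the boost arises only if the sentence is applied literally and non-glioblastoma deaths form a larger share of deaths in that arm. Under the assumed 10% against 2%, a true hazard ratio of 1.00 would read about 0.92. With equal shares there is essentially no bias, and the cost is a few points of power or a later analysis. A reader might infer that the plan as a whole favours the boost; without any rate in the documents, that is not established.

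The start of the clock at pathological confirmation is a minor note. It adds event-free lead time to the reported medians in both arms. The amount is unstated and is at most roughly the 8-week surgery-to-radiotherapy limit. Randomisation balances it, and the log-rank test is essentially unchanged. A reader might infer a conflict with intention-to-treat, but that principle fixes who is analysed and in which arm, not the time origin. Nor can it be said that the sample-size assumptions use a different clock, since the origin of the 16- and 24-month medians is not given.

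**What to change.** Replace the censoring sentence under Overall survival with: *The OS event is death from any cause. All patients not known to have died, including those lost to follow-up, are censored at the date last known alive.* Correct the parallel wording under Progression-free survival so that lost patients are covered explicitly there too. Make both changes before any unblinded look at the data.

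As an optional refinement, measure OS from randomisation and report survival from pathological confirmation descriptively if it is wanted for comparison with published series.

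The cost is a one-sentence change for each endpoint. The event target, sample size and stopping boundaries stay as they are. Moving the origin would shorten the reported medians slightly in both arms.

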#### Progression-free survival

PFS will be defined as the time between the first day of treatment and the date of disease recurrence confirmed by imaging (either on routine follow-up or symptom-directed imaging studies). Patients who do not succumb or who are not lost to follow-up and present with no evidence of disease progression will be censored at the date of the last follow-up.

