### Treatment response assessments

#### Imaging

To assess the initial responses to the CIRT boost, MET/FET PET or MRS will be performed at 2 weeks after the initiation of CIRT in the experimental arm. To assess the overall treatment response, MET/FET PET or MRS will be performed at 4 weeks after the completion of PRT in both arms. The target lesion will be evaluated using the response assessment in neuro-oncology (RANO) criteria [43] with interpretation modifications [44, 45] and is summarized below:Complete response (CR): Complete disappearance of all tumors on consecutive computed tomography (CT) or MRI scans sustained for at least 1 month, without the use of steroids.Partial response (PR): An observed ≥ 50% decrease in the area of contrast enhancement on consecutive CT or MRI sustained for at least 1 month. Doses of steroids must be stable or decreased, and the patient must be neurologically stable.Progressive disease (PD): An observed ≥ 25% increase in the area of contrast enhancement or any new tumor on CT or MRI.Stable disease (SD): All other situations.

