#### Analytical techniques

##### Outcome analyses

The difference in duration of survival between the two arms will be tested with a two-sided, stratified log-rank test at the 5% α level. Kaplan–Meier curves will be displayed, and median survival estimates and confidence limits will be calculated. The Cox regression analyses, adjusted and unadjusted, for stratification factors will be performed in an exploratory manner. PFS will be analyzed analogously to the method for OS, but of explorative nature.

A Lan-DeMets α spending function with an O’Brien-Fleming boundary will be used at the interim analysis to maintain an overall α of 0.05. The interim analysis will be performed after 96 OS events with an α of 0.003; the primary OS analysis will be performed after 192 events with an α of 0.049.

The rates of adverse events will be summarized by the type and severity. A Fisher’s exact test will be used to compare the observed adverse events between the two arms.

The primary efficacy analysis will be performed in the intention-to-treat (ITT) population, which is defined as the population of all randomized patients, analyzed in the arm to which they have been assigned. The OS and PFS of the ITT population will be calculated. The toxicity analysis will be performed on all patients who have received at least one dose of irradiation.

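### The PFS definition gives no outcome to a death without imaged progression and no start date to a randomised patient who is never treated, although PFS is promised for the ITT population.

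*Protocol article*

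**What the plan says.** Under Clinical outcome assessments, the Progression-free survival paragraph of the protocol article defines PFS as the "time between the first day of treatment and the date of disease recurrence confirmed by imaging". It accepts imaging done at routine follow-up or prompted by symptoms. The only other rule is for censoring, at the date of last follow-up: "Patients who do not succumb or who are not lost to follow-up and present with no evidence of disease progression will be censored".

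The Outcome analyses section states that "The OS and PFS of the ITT population will be calculated". It describes the ITT population as one "which is defined as the population of all randomized patients, analyzed in the arm to which they have been assigned". Receipt of at least one dose of irradiation is required only for the toxicity analysis.

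On the standing of the endpoint, the Phase III objectives say "The secondary objectives are to determine the response rates, progression-free survival (PFS), and tumor response", and Outcome analyses says "PFS will be analyzed analogously to the method for OS, but of explorative nature". The Biomarker analyses section uses PFS again, for comparisons by *MGMT* status and serologic marker level.

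**The concern.** Two rules fail when they are applied to particular patients.

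First, a patient who dies with no scan showing progression does not meet the event clause, which asks for imaging. Nor does that patient meet the censoring clause, which is limited to people who have not died. Two analysts could code the same patient differently. If the event clause is taken at its word and the death is handled as a non-event, the analysis is of time to imaged progression, not PFS. The trial adds a radiation boost and asks explicitly whether it brings extra toxicity. An endpoint that can lose early deaths could therefore hide a difference between the arms that matters.

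Second, a patient who is randomised but never treated has no first treatment day. The PFS time cannot be calculated, yet the patient belongs to the population for which PFS is promised. Leaving such patients out would turn the ITT analysis into an analysis of treated patients without saying so.

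**Working it through.** **The plan's own figure.** No event count, power or sample size is stated for PFS. The only related figure is the 192 OS events for medians of 16 and 24 months. Schoenfeld's formula with 1:1 allocation gives 4 × (1.960 + 0.842)² / (ln(16/24))² = 31.40 / 0.1644 ≈ 191, and power at 192 events is 80.2%. The figure reproduces, and it does not depend on how PFS is defined.

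**Deaths: the clauses side by side.**

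| Patient at last contact | Event clause | Censoring clause |
|---|---|---|
| Imaged progression, alive or later dead | event | not needed |
| Alive, in follow-up, no progression | no | censored |
| Dead, no imaged progression | no | no |

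The third row has no outcome. For contrast, the Overall survival paragraph just before it expressly ends its clock at death from any cause.

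**Start date: the sections side by side.** PFS runs from the first treatment day. The ITT set is everyone randomised. The Treatment assignment section foresees withdrawals in Phase III and lets withdrawn patients keep their randomisation number, so they remain in that set. One who withdraws before any irradiation has no PFS start date. OS does not share this gap: it runs from pathological confirmation, and histological confirmation is an inclusion criterion.

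**Illustration of size. All PFS inputs here are assumptions; the document gives none.** Take exponential times, a median time to imaged recurrence of 7 months with hazard λ, and a share s of first events that are deaths without imaged recurrence. The hazard with deaths counted is λ/(1 − s), so the median is 7 × (1 − s).

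| s | Median, deaths censored (months) | Median, deaths counted (months) |
|---|---|---|
| 5% | 7.0 | 7 × 0.95 = 6.65 |
| 10% | 7.0 | 7 × 0.90 = 6.30 |
| 20% | 7.0 | 7 × 0.80 = 5.60 |

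If the recurrence hazard is the same in both arms, the hazard ratio (experimental to control) with deaths censored is 1.00. With deaths counted it is (1 − s_control)/(1 − s_exp):

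- s of 10% in control and 20% in experimental: 0.90/0.80 = 1.125.
- s of 10% in both arms: 1.00.

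The comparison between arms is therefore distorted only if the share differs by arm.

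For the start date, assume that 1%, 3% or 5% of the 243 patients are never treated: 2.4, 7.3 or 12.2, or about 2, 7 or 12 patients. The planned 5% dropout is no estimate of this, since it combines loss to follow-up with treatment discontinuation.

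**The case against.** The strongest reply is that the censoring sentence, by speaking only of patients who have not died, shows that deaths were meant to count. That is plausible. A reader might infer from the event clause that the plan treats deaths as non-events and so makes PFS too long, but the text does not go that far. What stands is that the two clauses do not fit together and the death has no assigned outcome. The bias follows only on one of the two readings.

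It can also be said that MRI at every follow-up visit, together with symptom-directed imaging, should keep deaths without imaged progression uncommon. That bears on the size of the gap, which the document does not allow anyone to estimate. It does not supply the missing rule.

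Three further criticisms are tempting, but the document does not support them:

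- *The scan done only in the boost arm could date events in that arm alone.* The Imaging section says "MET/FET PET or MRS will be performed at 2 weeks after the initiation of CIRT in the experimental arm". That scan serves to assess the initial response to the boost. It is neither routine follow-up, which begins 1 month after radiotherapy, nor symptom-directed. It is PET or MRS, while progressive disease is defined there on CT or MRI. As written, it would not date a PFS event.
- *The start date shifts the experimental arm's scans by a week.* Proton therapy starts one week after the first boost fraction and follow-up is timed from the end of radiotherapy. With equal delay to treatment, the shift would remain if the clock started at randomisation. It is also small against 3-monthly visits.
- *Recurrence is the wrong event, because eligibility requires "Residual, clinically measurable tumor up to 5 cm in the largest dimension".* This is terminology. The censoring sentence itself speaks of progression, and the Imaging section defines progressive disease.

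**Conclusion.** The point holds in two parts, both on the text alone. A death without imaged progression has no PFS outcome, and a randomised but untreated patient has no PFS start date although PFS is promised for the ITT population. These are rules that the article states, not details that it leaves to a fuller document.

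The reach is limited. PFS is secondary and explorative and has no alpha or sample size of its own. OS counts death from any cause, so the 192 events, the 243 patients and the primary conclusion are untouched. A reader might try to derive a number of lost PFS events by applying a percentage to the 192 deaths. That would not be sound, because 192 is the trigger for the OS analysis and the document gives no such percentage. The hazard ratio of 1.125 and the range of 2 to 12 patients show how the gaps could act under assumed inputs; they are not estimates for this trial. The definition should still be corrected, because PFS is a named Phase III endpoint, is reused in the biomarker analyses, and costs almost nothing to repair.

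**What to change.** Replace the PFS definition with:

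> PFS is the time from randomisation to first progression (PD as defined under RANO in the imaging section) or death from any cause, whichever comes first, in all randomised patients; patients alive without progression are censored at the last tumour assessment.

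This gives every death an outcome and every randomised patient a start date, and it matches the ITT statement in Outcome analyses. Since each follow-up visit includes a brain MRI, the censoring date should usually be the same as under the present rule.

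The cost is wording only: no extra scans, patients or visits. The net effect on the reported median PFS is not known. Counting deaths shortens it (or leaves it as it is, if deaths were already going to be counted), while starting at randomisation lengthens it, and the document gives neither quantity.
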